## Abstract

**Background:**

Anaemia is a common complication of chronic kidney disease and prevalence increases with declining renal function. Renal anaemia has significant implications for the well-being and quality of life of patients and impacts on morbidity and mortality. Anaemia can be well managed by therapy with erythropoiesis-stimulating agents (ESAs). Previous clinical trials have shown that the only human cell-line-derived ESA, epoetin delta, is well tolerated and effective in maintaining haemoglobin levels in anaemic patients with chronic kidney disease. The half-life of epoetin delta suggests that administration of this agent is feasible once weekly and once every two weeks. We report on the design and rationale of a trial to compare once weekly *vs*. twice weekly, and once weekly *vs*. once every two weeks dosing of epoetin delta.

**Design and methods:**

This is a randomized, open-label, multicentre trial. Patients aged 18 years or above with chronic kidney disease (Stages 3–5) are eligible to enter this trial. Two groups of patients form the trial population, those naïve to ESA therapy and those previously stable on ESA therapy. There are two primary objectives of this trial: 1) to demonstrate non-inferiority between twice weekly and once weekly dosing of epoetin delta in previously naïve patients (assessed by haemoglobin at Week 24); 2) to demonstrate non-inferiority between once weekly and once every two weeks dosing in previously stable patients (assessed by average haemoglobin over Weeks 16–24). Among the secondary analyses will be assessments of haematocrit, number(%) of patients meeting predefined targets for haemoglobin and haematocrit levels, and comparisons of average dose. All patients will receive study medication for 24 weeks and dose will be adjusted according to a predefined algorithm to achieve and maintain haemoglobin ≥ 11 g/dL. All patients completing this trial are eligible to enter a 2-year follow-up study to enable monitoring of emergent adverse events, anti-erythropoietin antibody responses, maintenance of efficacy and changes in diabetic retinopathy status.

**Discussion:**

To our knowledge, this trial is the first to randomize ESA-naïve patients to different dosing regimens of the same ESA. Data generated will help in guiding the most appropriate dosing frequency for epoetin delta, particularly in those patients new to epoetin delta therapy.

**Trial registration:**

**ClinicalTrials.gov: **NCT00450333

## Background

Chronic kidney disease (CKD) is a growing problem, particularly in the Western world [1] and anaemia is a common complication of CKD, with up to half of all patients affected [2]. Diabetes is the leading cause of CKD in the Western world and in diabetic CKD patients anaemia often develops earlier and more severely than in non-diabetic patients with similar renal function [3,4]. As kidney function declines the prevalence of renal anaemia increases, with most CKD Stage 5 patients (glomerular filtration rate <15 mL/min/1.73 m^2^), on or off dialysis, being anaemic [5]. The primary cause of anaemia in CKD patients is insufficient synthesis of erythropoietin by the damaged kidneys. Anaemia is associated with fatigue and reduced quality of life [6] as well as increased morbidity and mortality [7-9], often due to cardiovascular complications [10]. In addition, anaemia in diabetic patients has been linked with the progression of microvascular complications, including retinopathy [11,12]. Renal anaemia can be managed by treatment with erythropoiesis-stimulating agents (ESAs), which are effective and well-tolerated [8].

The original recombinant erythropoietins (epoetin alfa and epoetin beta) are produced in Chinese hamster ovary cell lines. In contrast, epoetin delta is produced in a human cell line, via a process of gene-activation [13]. Clinical trials have demonstrated that epoetin delta is well tolerated and effective in the management of renal anaemia in CKD patients irrespective of dialysis status or dose frequency [14-17].

In a previous clinical trial epoetin delta administered subcutaneously was shown to be effective in predialysis, peritoneal dialysis and haemodialysis patients [14]. In this trial, epoetin delta administered two- or three-times per week was effective and well tolerated in patients irrespective of dialysis status (predialysis, peritoneal dialysis, haemodialysis). Administration once per week was effective in maintaining haemoglobin levels in predialysis and peritoneal dialysis patients [14,17]. Phase I and II studies of subcutaneous epoetin delta [18] showed that the half-life was similar to that of epoetin beta, an agent that can be administered once per week [19,20]. Patients who are stable on a once weekly dosing regimen with subcutaneous epoetin beta can be switched to once every 2 weeks administration [21]. The combined evidence from clinical trials indicates that it may be possible to extend dosing intervals for epoetin delta beyond once per week. We report on the design and rationale of a trial to assess this potential, highlighting its unique aspects.

## Design and methods

### Design and objectives

This is a multicentre, open-label, randomized, parallel-group study, designed to provide information on extended intervals of dosing with epoetin delta (DYNEPO^®^, Shire plc) in the management of renal anaemia. New dosing regimens will be explored for patients naïve to ESA therapy and patients already stable on ESA treatment.

Two primary objectives have been set for this trial:

1. To demonstrate non-inferiority between twice-weekly (BIW) and once-weekly (QW) dosing of epoetin delta in previously ESA-naïve patients, as assessed by haemoglobin at Week 24

2. To demonstrate non-inferiority between QW and once every two weeks (Q2W) dosing in patients previously stable on an ESA, as assessed by average haemoglobin over Weeks 16–24.

Several secondary objectives, including a key secondary objective, have been included in the trial design and these are detailed below.

Key secondary objective: to demonstrate non-inferiority of efficacy between QW and Q2W dose schedules in patients previously stable on an ESA, as measured by average dose over Weeks 16–24.

Other secondary objectives:

1) To compare efficacy between BIW and QW dose schedules of epoetin delta in previously ESA-naïve patients and between QW and Q2W dose schedules in patients previously stable on an ESA, as measured by:

a) the number (%) of patients who achieve haemoglobin of ≥ 11 g/dL at Weeks 16 and 24 and over Weeks 16–24.

b) haematocrit at Weeks 16 and 24, and over Weeks 16–24.

c) the number (%) of patients achieving the haematocrit target range of 33–36% at Weeks 16 and 24 and over Weeks 16–24.

d) the number (%) of patients who achieve both haemoglobin and haematocrit targets (≥ 11 g/dL and 33–36% respectively) at Weeks 16 and 24 and over Weeks 16–24.

2) To compare the average dose over Weeks 9–16, 16–24 and 9–24 between BIW and QW dose schedules of epoetin delta in previously ESA-naïve patients and between QW and Q2W dose schedules in patients previously stable on an ESA.

3) To compare efficacy between BIW and QW dose schedules of epoetin delta in previously ESA-naïve patients as measured by haemoglobin at Week 16 and over Weeks 16–24.

4) To compare efficacy between QW and Q2W dose schedules in patients previously stable on an ESA as measured by haemoglobin at Weeks 16 and 24.

5) To investigate safety of:

a) BIW and QW dose schedules in previously ESA-naïve patients.

b) QW and Q2W dose schedules in patients previously stable on an ESA.

6) To investigate efficacy and safety of epoetin delta when switching administration frequencies.

7) To summarize efficacy and safety in patients with diabetes mellitus (DM).

### Ethical considerations

This trial will be conducted in agreement with the current applicable regulations, ICH, EU Directive 2001/20/EC, principles of the Declaration of Helsinki and approved by the relevant review board for all participating study centres. All patients will give written informed consent before completing any study-related procedures.

### Study groups

Patients are grouped by previous exposure to an ESA and randomized to differing dose schedules. Group 1 is formed by ESA-naïve patients, Group 2 by patients previously stable on ESA therapy (Figure 1). Patients in both groups are stratified by dialysis status to balance expected adverse event levels. All participants will be ≥ 18 years of age, with anaemia due to CKD (Stages 3–5; GFR < 59 mL./min/1.73 m^2^). The major inclusion and exclusion criteria are shown in Table 1. It is planned to include 208 patients in each arm, randomizing 104 to each dosing regimen, giving a total patient number of 416.

**Figure 1 F1:**
[figure not shown]
Trial design.

**Table 1 T1:** Major selection criteria

**Inclusion criteria**
• Patients aged at least 18 years of age with CKD (KDOQI Stage 3–5) who are able to give written informed consent and are likely to attend all study visits • Stable on any dose ≤ 10 000 IU/week of subcutaneous ESA or requiring initiation of ESA treatment • Those currently receiving ESA treatment must have been receiving a stable dose, that was effective in managing haemoglobin levels (≥ 11 g/dL), for at least 30 days before randomization in the study • Those requiring initiation of ESA treatment must have haemoglobin levels ≥ 8 g/dL and < 11 g/dL • Transferrin saturation ≥ 20 % and ferritin ≥ 100 ng/mL

**Major exclusion criteria**

• Uncontrolled hypertension • Requiring doses of ESA > 10 000 IU/week • Two or more doses of prescribed ESA treatment missed or withheld by physician order in the 14 days immediately before randomization in the study • Thrombocytopenia (platelet count < 75 000/mm^3^) • Active bleeding disorder (diathesis) (for example, gastro-intestinal or genito-urinary tract bleeding) • Treatment with immunosuppressive drugs (other than corticosteroids for a chronic condition) in the 30 days immediately before randomization in the study • Androgen therapy in the 30 days immediately before randomization in the study • Known HIV infection from medical history • Known or suspected intolerance or hypersensitivity to ESA therapy or to any of the excipients of epoetin delta • Known to have antibodies against erythropoietin • Impaired hepatic function (AST, ALT > 3x ULN)

### Study treatments

All patients will receive epoetin delta, administered subcutaneously, for a maximum of 24 weeks. Dose is adjusted to achieve and maintain haemoglobin ≥ 11 g/dL. If haemoglobin is ≥ 12 g/dL OR the rate of increase of haemoglobin is > 2.5 g/dL/4-week period then the dose is decreased by 25%. If haemoglobin is < 10 g/dL AND the rate of increase is < 0.7 g/dL/4-week period then the dose is increased by 50%. Patients in Group 1 will start on 100 IU/kg/week, and patients in Group 2 will start on a weekly dose of epoetin delta equivalent to the dose of ESA they were previously receiving to maintain stability.

Patients will receive a maximum dose of 20 000 IU at any one time. If the dose schedule determines that they should receive > 20 000 IU they will be withdrawn from their randomized arm and followed for safety in a non-responder rescue group, where their dose of epoetin delta will continue to be adjusted towards a stable dose on a schedule that allows for doses of ≥ 20 000 IU at any one time.

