### Statistical methods

416 patients will be included in this study (208 naïve and 208 non-naïve). The primary endpoint for this study is haemoglobin (g/dL) at Week 24 for ESA-naïve patients and average haemoglobin over Weeks 16–24 for patients previously stable on an ESA. Based on a similar study [14] and assuming the true difference between dose schedules is zero (using a non-inferiority margin of 0.75 g/dL), 65 patients in each arm are required to complete the trial without major protocol violations to provide 90% power. Full criteria for evaluation are shown in Table 3.

**Table 3 T3:** Criteria for evaluation

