**Secondary objectives**

• Number (%) of patients who achieve haemoglobin of ≥ 11 g/dL at Weeks 16 and 24 and over Weeks 16–24 • Mean haematocrit concentration calculated at Weeks 16 and 24 and over Weeks 16–24 • Number (%) of patients who achieve the haematocrit target range of 33–36% at Weeks 16 and 24 and over Weeks 16–24 • Patients' average weekly dose/kg over Weeks 9–16, 16–24 and 9–24 • Mean haemoglobin concentration calculated at Week 16 • Number (%) of patients who achieve both haemoglobin of ≥ 11 g/dL and the haematocrit target range of 33–36% at Weeks 16 and 24 and over Weeks 16–24 • Number (%) of patients with a positive antibody response to epoetin delta • Number (%) of patients shown to have neutralizing antibodies • Blood pressure changes from baseline • Changes in left ventricular ejection fraction from the screening visit • Renal function using estimated glomerular filtration rate • Retinopathy in diabetic patients

ANCOVA analysis will be used for the endpoint of mean haemoglobin at Week 24 in each dose group for the ESA-naïve patients (QW and BIW). A 95% confidence interval (CI) for the difference between QW and BIW in mean haemoglobin will be calculated and non-inferiority of QW compared with BIW will be concluded if the lower limit of the 95% CI lies above -0.75 g/dL. For the endpoint of average haemoglobin over Weeks 16–24 in each dose group for previously stable patients (QW and BIW), repeated measures ANCOVA analysis will be used. A 95% CI for the difference between Q2W and QW in mean haemoglobin will be calculated and non-inferiority of Q2W compared with QW will be concluded if the lower limit of the 95% CI lies above -0.75 g/dL. These results will be assessed in both per-protocol and intent-to-treat populations. All patients who receive study medication will be included in the safety analyses.

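### In Group 2 the 20 000 IU per-injection limit takes failing patients out of their arm almost only on once-every-two-weeks dosing, which can favour non-inferiority of that schedule

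*Protocol article*

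**What the plan says.** All of this is in the protocol article.

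- **Limit.** Study treatments: "Patients will receive a maximum dose of" 20 000 IU in a single administration, whatever the schedule. Of patients who would need more: "they will be withdrawn from their randomized arm and followed for safety in a non-responder rescue group". Their dose is then titrated further on a schedule that permits larger injections.
- **Starting dose.** Study treatments: "patients in Group 2 will start on a weekly dose of epoetin delta equivalent to the dose of ESA they were previously receiving". This applies to both Group 2 arms.
- **Entry ceiling.** Table 1 admits patients stable on at most 10 000 "IU/week of subcutaneous ESA or requiring initiation of ESA treatment". Those already on treatment must have haemoglobin of at least 11 g/dL.
- **Dose increase.** Study treatments: "If haemoglobin is < 10 g/dL AND the rate of increase is < 0.7 g/dL/4-week period then the dose is increased by 50" per cent.
- **Decision rule.** Statistical methods, Group 2: "non-inferiority of Q2W compared with QW will be concluded if the lower limit of the 95% CI lies above -0.75 g/dL". On populations: "These results will be assessed in both per-protocol and intent-to-treat populations".
- **Key secondary objective.** Design and objectives: non-inferiority of Q2W to QW on average dose over Weeks 16–24.
- **Endpoints.** Statistical methods: "Full criteria for evaluation are shown in Table 3". That table has no count of patients moved to rescue.

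**The concern.** The limit is set per injection, but the two Group 2 arms are matched on weekly dose. The same limit therefore stops a Q2W patient at half the weekly dose that a QW patient may reach. A patient reaches it only through a raise, and a raise is given only when haemoglobin is low and responding poorly. The patients who leave are thus failures of their schedule, and nearly all would be on Q2W, the schedule for which non-inferiority is to be shown.

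The printed sentence takes these patients out of their randomized arm and gives safety as the purpose of follow-up. If that is followed literally, low haemoglobin values leave the Q2W arm before or during Weeks 16–24. The average dose seen on Q2W is also cut off at 10 000 IU/week. Both effects make Q2W look closer to QW than it is in all randomized patients.

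**Working it through.** **Inputs from the article.** 20 000 IU per injection, raise of 50%, raise criteria and equal weekly starting dose (Study treatments); entry ceiling 10 000 IU/week and entry haemoglobin ≥ 11 g/dL (Table 1); margin 0.75 g/dL, two-sided 95% CI, 65 evaluable patients per arm, 90% power (Statistical methods); 104 randomized per regimen (Study groups).

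**1. The plan's own figure.** The SD behind 65 per arm is not printed. Solving for it: SD = 0.75 × √(65/2) / (1.960 + 1.282) = 1.32 g/dL. For comparison, an SD of 1.2 needs 54 per arm, 1.3 needs 64 and 1.4 needs 74. So 65 can be neither confirmed nor refuted. The dose argument does not depend on it; 1.32 is used below as an assumption.

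**2. The limit in weekly terms.** Weekly limit = 20 000 / weeks between injections. A patient passes it at raise k if the entry dose exceeds the weekly limit / 1.5^k, with no dose reduction in between.

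| | QW | Q2W |
|---|---|---|
| Weekly limit (IU/week) | 20 000 / 1 = 20 000 | 20 000 / 2 = 10 000 |
| Leaves at first raise if above | 20 000 / 1.5 = 13 333 | 10 000 / 1.5 = 6 667 |
| Leaves by second raise if above | 20 000 / 2.25 = 8 889 | 10 000 / 2.25 = 4 444 |

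No eligible QW patient can leave at the first raise from the entry dose, because 10 000 × 1.5 = 15 000. A patient entering at 8 000 IU/week leaves at the first raise on Q2W and at the third on QW.

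**3. Who leaves.** No eligible patient starts above the limit (10 000 × 2 = 20 000), so every exit needs a raise. Everyone who leaves therefore entered at ≥ 11 g/dL and has fallen below 10 g/dL with a rise under 0.7 g/dL per 4 weeks.

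**4. Direction if they are dropped.** Let a fraction f of Q2W leave, with mean haemoglobin g below those who stay. Dropping them raises the Q2W mean by f × g. Take a true difference of −0.75 g/dL and SE = 1.32 × √(2/65) = 0.2315. The chance of wrongly concluding non-inferiority is then Φ(f × g / SE − 1.96), against 2.5% with no exits.

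| f (assumed) | g (assumed, g/dL) | Shift (g/dL) | False conclusion |
|---|---|---|---|
| 5% | 1.0 | 0.05 | 4.1% |
| 10% | 1.5 | 0.15 | 9.5% |
| 20% | 2.0 | 0.40 | 41% |

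**5. Three ways of treating the exits.** A simulation applied the printed algorithm and limit. Its inputs are assumptions: entry haemoglobin mean 11.5–12.5 g/dL, dose-response slope 1.5–3.5 g/dL per log-dose, 14–42% of patients entering above 6 667 IU/week. Pass rate = Φ((0.75 + difference)/0.2315 − 1.96). For example, a difference of −0.29 gives 0.46/0.2315 − 1.96 = 0.03, or 51%.

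| Handling | 20–25% of Q2W lose 2.5–3 g/dL: difference (pass rate) | Uniform 1.0 g/dL loss: difference |
|---|---|---|
| Only those remaining | +0.01 to −0.29 (51–91%) | −0.04 to −0.60 |
| All patients, rescue titration continued | +0.02 to −0.37 (38–92%) | −0.03 to −0.62 |
| Last pre-exit value kept | −0.04 to −0.40 (32–87%) | −0.06 to −0.66 |

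In the first pattern 4–16% of Q2W leave (about 4–17 of 104) against at most 0.1% of QW. With the uniform loss, 2–14% of Q2W leave. The sample size already allows for 104 − 65 = 39 losses per arm, so exits on this scale would not stand out.

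**6. Dose.** On-arm dose cannot exceed 10 000 IU/week on Q2W but can reach 20 000 on QW. In the first pattern the Q2W/QW dose ratio is 1.04–1.23 in those remaining, against 1.20–1.39 in all patients had there been no limit.

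**The case against.** The limit is a reasonable safety rule and arguably part of the Q2W regimen. The sentence on withdrawal stands in the treatment section and does not say that haemoglobin is discarded or that patients leave the analysis sets. An intent-to-treat analysis is planned beside the per-protocol one. Rescue dosing continues to be titrated, and the printed titration rules run on haemoglobin, so haemoglobin would presumably still be measured. How such values enter the analysis may be set out in a full protocol or SAP that is not shown. Table 3 does not list adverse events either, so a missing rescue count in a condensed article is not in itself an error.

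Most of this stands, and it rules out three stronger readings.

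- A reader might infer that both planned analyses are compromised to the same degree. The figures do not support that. With rescue titration continued in all patients, the pass rate is 38–92%, close to the 32–87% when the last value is kept; the ends of the two difference ranges lie only 0.03–0.06 g/dL apart.
- A reader might take the gap between those remaining and the last-value analysis (4 to 46 points of pass rate, median about 20) as the size of the bias. That gap rests on a loss pattern that nothing in the article supports, and it leaves out the intent-to-treat analysis.
- A reader might conclude that the last value below 10 g/dL should stand for Weeks 16–24 in the main analysis. That is one defensible choice among several: a QW patient with the same value would receive a raise and might recover.

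The objection does not remove the printed rule itself. It assigns these patients out of their arm, and an SAP that kept them in would have to work against that sentence.

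**Conclusion.** The point holds in limited form and should be corrected. The 2:1 difference in weekly limit, its coincidence with the entry ceiling on Q2W, and the link between exit and low haemoglobin all follow from the article alone. Followed as printed, the rule can bias the per-protocol haemoglobin comparison and the on-arm average-dose comparison towards non-inferiority of Q2W.

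The size is not established. It depends on the entry-dose distribution, the dose response and how often Q2W fails, none of which the article gives. It also depends on reading the per-protocol set as excluding patients withdrawn from their arm, which is the natural reading but is not stated. The effect is smaller if intent-to-treat uses haemoglobin measured after rescue. If Q2W is truly equal, the simulation has only 0.2–2.4% of Q2W leaving. The dose ratios compare with a trial without the limit, which nobody proposes, and no ratio including rescue doses was calculated; they show direction only.

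**What to change.** Keep the limit, the algorithm, the margin and the entry criteria.

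1. Reword the withdrawal sentence in Study treatments along these lines: *A patient whose schedule would require more than 20 000 IU in one injection stops the randomized schedule and is treated in the rescue group, but remains in the randomized arm for the Group 2 comparison. Haemoglobin and dose are recorded through Week 24 and included in the intent-to-treat analysis.*
2. Add to Table 3 the number (%) moved to rescue by arm, with a 95% CI for the difference, and show it beside the haemoglobin and dose results.
3. Add a sensitivity analysis, the same in both arms, that carries the last haemoglobin before exit through Weeks 16–24. Read non-inferiority of Q2W together with it.

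**Cost.** A reworded sentence, a table row and one further analysis. The pre-exit haemoglobin is already measured at the visit that triggers the exit; continued collection to Week 24 adds little if rescue titration is guided by haemoglobin. If Q2W is truly equal, the simulated difference with the last value kept is 0.00 to −0.03 g/dL, so power in the sensitivity analysis falls from 90% to 87–90% at 65 per arm. The change would come after enrolment began: 158 of 416 by 18 October 2007, of whom 158 − 43 = 115 were not ESA-naïve. It should therefore be fixed without reference to results by arm.

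The alternatives cost more. An equal limit of 10 000 IU/week would take QW patients off doses they may now receive, and an entry ceiling of 6 667 IU/week would narrow recruitment.
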